### Randomization and allocation

The spinal needle that will be used in the patient’s first study LP procedure, either the IQ-Tip system (study arm A) or a conventional spinal needle (study arm B), was determined by block randomization before recruiting patients. Block randomization ensures an approximately even number of both sequences of study LP procedures (ABAB and BABA) in random order while eliminating the bias that may arise from a fixed order of LP procedures.

With a dedicated Matlab script, the sponsor has generated randomization lists for each investigational site beforehand (date 30/09/2022). The sponsor will also prepare and deliver enough sequentially numbered sealed envelopes containing the randomly assigned sequences (either ABAB or BABA) to the investigational sites. During the trial, the person who will perform the statistical analyses will not meet the participants nor be involved anyhow in collecting data or filling their case report forms (CRF).

Upon enrolling a new patient to the study, the next available envelope in the order will be opened to reveal the sequence of study LP procedures for the given patient. This sequence determines the choice of a specific Participant’s File, a binder that contains color-coded CRFs and other relevant documents for collecting the data from the four study LP procedures. The running number of the envelope together with the hospital-specific three-letter prefix will determine the patient’s pseudonym (ID code).

### Procedures

The study LP procedures will be performed either with the IQ-Tip system (study arm A) or the conventional spinal needle (study arm B) according to the patient’s randomly allocated sequence. The personnel of the investigational sites will perform the study LP procedures within the usual clinical workflow. As a standard procedure, the LP procedures of pediatric patients with leukemia are performed under general anesthesia in the lateral decubitus position [19]. Because of general anesthesia, the patient is blinded to the allocated spinal needle. As both study needles are similar, the need for unblinding is deemed irrelevant.

Before starting the study, the sponsor’s representatives will give an overview of the Instructions for Use and a practical training session on the use of the IQ-Tip system to the local principal investigators ([name]), other physicians, and study nurses at the investigational sites. The attendees will also have the possibility to try the system on a lumbar phantom (Blue Phantom BPLP2201, CAE Healthcare, FL, USA). Later, the local principal investigators will be responsible for the training of new users of the system.

The above-described short training was employed in our previous single-arm study [19]. Immediately after that study, the usability of the IQ-Tip system was assessed with System Usability Scale (SUS) [28, 29]. In short, all 26 physicians who had performed at least one study LP procedure with the IQ-Tip system received an electronic SUS form, 20 of them (77%) responded anonymously. The mean SUS score was 75 (SD 13), which indicates good clinical usability and acceptability for the system.

#### The LP procedure A

Study procedure A will be performed with the IQ-Tip system (Injeq Plc, Tampere, Finland), which is a CE-marked medical device as per Medical Device Regulations (MDR EU 2017/745) approved for any clinically indicated LP procedure. The system comprises either a 40-mm, 65-mm, or 90-mm-long 22G Quincke-type spinal needle (IQ-Tip spinal needle), a bioimpedance analyzer, and a thin, flexible coaxial cable for connecting the needle to the analyzer. The IQ-Tip spinal needle is identical to the conventional Quincke-type 22G spinal needle with a stylet, except the stylet is configured as a bioimpedance electrode and it has a cable connector at the handle end. The analyzer has an internal memory, where the raw bioimpedance data collected at a 200-Hz sampling rate will be stored for further post-hoc analysis.

Performing the LP procedure with the bioimpedance needle is basically like that with the conventional spinal needle. Also, the removal and reinsertion of the stylet do not differ from the conventional spinal needle. Only the cable at the handle end is the major difference.

When performing the LP procedure with the IQ-Tip system and perceiving the CSF detection alarm, the provider can either remove the stylet and check for CSF flow through the needle or continue the puncture upon clinical judgment on the location of the needle tip. Similarly, irrespective of the alarm, the provider can remove the stylet and check for CSF flow whenever considered necessary.

When the needle tip is correctly in the subarachnoid space verified by CSF flow, the provider will take the CSF sample and deliver the intrathecal therapy according to the patient’s treatment protocol.

Right after performing the study LP procedure with the IQ-Tip system, the provider will evaluate the performance and record the results concerning a successful procedure at the first attempt, number of attempts needed for a successful procedure, number of stylet removals in the successful procedure, failure to perform the procedure, and the accuracy of perceived alarms on the patient’s CRF. Also, patients’ immediate complications and device deficiencies, if any, will be recorded on CRF.

#### The LP procedure B

Study LP procedure B will be performed with a conventional 22G Quincke-type spinal needle according to the standard clinical practices of the investigational sites.

When performing the LP procedure with the conventional needle, the provider can, upon clinical judgment on the location of the needle tip, remove the stylet and check for CSF flow through the needle, or continue the puncture.

When the needle tip is correctly in the subarachnoid space verified by CSF flow, the provider will take the CSF sample and deliver the intrathecal therapy according to the patient’s treatment protocol.

Right after performing the study LP procedure with the conventional needle, the provider will evaluate the performance and record the results concerning successful procedure at the first attempt, total number of attempts needed for a successful procedure, number of stylet removals in the successful procedure, and failure to perform the procedure on the patient’s CRF. Also, patients’ immediate complications and device deficiencies, if any, will be recorded on CRF.

### Outcomes

#### Primary outcome

The primary outcome is the incidence of TLP, which is defined as ≥ 10 erythrocytes/μL of the CSF sample, conforming to the standard definition in hemato-oncology [4–14]. Hospital laboratories will routinely determine the red blood cell count (erythrocytes/ μL) from CSF with flow cytometric methods according to their standard procedures.

The incidence of TLP will be separately calculated for both study arms using Eq. 1.1$$\mathrm{Incidence\;of\;TLP}=100\times \frac{\mathrm{Total\;number\;of\;TLPs}}{\mathrm{Total\;number\;of\;all\;procedures}}\mathrm{\%}$$

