#### Secondary outcomes

Secondary outcomes are the first puncture success rate and the incidence of PDPH related to the LP procedures in both study arms.

The success of performing the procedure at the first attempt is defined by the following conditions: only one skin penetration with the needle is done, an eligible CSF sample is obtained and sent for the laboratory analysis, and/or the intrathecal therapy is delivered, and the primary provider does not change during the procedure. Multiple needle redirections are allowed provided that the needle tip remains beneath the skin. Multiple stylet removals and reinsertions are also allowed.

The percentage proportions of the first puncture success rate will be separately calculated for both study arms using Eq. 2.2$$\mathrm{First\;puncture\;success\;rate}=100\times \frac{\mathrm{Total\;number\;of\;succesful\;procedures\;at\;the\;first\;attempt}}{\mathrm{Total\;number\;of\;all\;procedures}}\mathrm{\%}$$

After each study LP procedure, the local study nurse or investigator will give the patient or parents a diary to be filled for reporting perceived symptoms or complications during the day of the procedure and seven subsequent days. These symptoms and complications include PDPH, headache, nausea, backache, fever, leaking, or inflammation at the puncture site. Conforming to the standard definition, PDPH is a severe headache that worsens in sitting or standing positions, eases after lying down, and occurs within 7 days after the procedure. After the week, the study nurse or investigator will contact the patient or parents and inquire about the diary data.

The incidence of PDPH will be separately calculated for both study arms using Eq. 3.$$\mathrm{Incidence\;of\;PDPH}=100\times \frac{\mathrm{Total\;number\;of\;procedures\;causing\;PDPH}}{\mathrm{Total\;number\;of\;all\;procedures}}\mathrm{\% }$$

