The number of attempts needed for a successful LP procedure will be recorded for each study procedure. Congruent with the definition of the first puncture success rate, an attempt denotes any new penetration of the skin. Being successful means that, irrespective of the number of attempts, a CSF sample is eventually obtained and/or the intrathecal therapy is performed as appropriate for the given procedure. The number of failed LP procedures will be registered as well. An LP procedure is considered failed if the physician(s), even after multiple attempts, conclude that the subarachnoid space cannot be verifiably reached, and the procedure remains incomplete with the available personnel or equipment due to any reason. Also, the provider’s decision to use other than the assigned spinal needle due to any reason is considered a failed procedure. These procedural outcomes will be reported for both arms.

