**Fig. 2 Fig2:**
[figure not shown]
Schematic on the relation between the numbers of traumatic LP procedures (TLP) with the IQ-Tip system and conventional spinal needle required to indicate noninferiority (green area) or not (red area)

The primary statistical comparison of outcome variables will be based on the true use of the allocated spinal needles in the study LP procedures. Therefore, per-protocol analysis will be employed in the efficacy analysis as recommended for noninferiority trials [32]. The incidences of TLP and PDPH as well as the first puncture success rate between the respective study arms will be compared with the Chi-squared test. The 95% confidence intervals (95% CI) for the difference will be calculated using the exact Clopper-Pearson method. Between-arm comparisons of blood and CSF data, other performance parameters, and incidences of other complications will be performed for descriptive purposes. Definitions of the outcome variables to be used in the efficacy analysis are presented in Table 2 in terms of domain, measurement, metric, aggregation, and time point according to a recommended framework for clinical trials [33, 34]. In case of missing data, data estimation nor imputation will not be performed.

**Table 2 Tab2:** Definitions of the outcome variables (only those domains pertinent to the efficacy analysis are presented) in terms of domain, measurement, metric, aggregation, and time point

Domain	Specific measurement	Metric	Method of aggregation	Time point
Incidence of TLP	Flow cytometry	Erythrocyte count ≥ 10/µL (yes/no)	Proportion	Each study LP procedure
First puncture success rate	Provider’s self-report on CRF	Occurrence (yes/no)	Proportion	Each study LP procedure
Incidence of PDPH	Symptom diary	Occurrence (yes/no)	Proportion	Within 1 week after each study LP procedure
Peripheral blood analysis	Flow cytometry	Erythrocyte count (cells/µL) Hematocrit (%) Hemoglobin (g/L) Leukocyte count (cells/µL) Thrombocyte count (cells/µL) Existence of blasts (yes/no)	Mean Mean Mean Mean Mean Proportion	Each study LP procedure
CSF analysis	Flow cytometry	Erythrocyte count (cells/µL) Leukocyte count (cells/µL) Existence of blasts (yes/no)	Cumulative distribution curve Mean Proportion	Each study LP procedure
Number of LP attempts	Provider’s self-report on CRF	Number	Median	Each study LP procedure
Number of failed procedures	Provider’s self-report on CRF	Occurrence (yes/no)	Proportion	Each study LP procedure

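### Eq. 1 divides TLPs by all procedures although TLP status needs a CSF erythrocyte count; taken literally, uncounted procedures act as non-traumatic, with a bias whose size and direction depend on how they split between arms

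*Protocol article*

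**What the plan says.** All references are to the protocol article.

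- **Primary outcome.** TLP is a CSF erythrocyte count of at least 10/μL. The source of the count is the hospital laboratory: "Hospital laboratories will routinely determine the red blood cell count". Then "The incidence of TLP will be separately calculated for both study arms using Eq" 1, whose denominator is all procedures in the arm.
- **Secondary outcomes.** First-puncture success requires that "an eligible CSF sample is obtained and sent for the laboratory analysis, and/or the intrathecal therapy is delivered". The and/or allows a successful procedure without a CSF sample. Other outcomes uses the same and/or for success after any number of attempts.
- **Other outcomes.** A procedure has failed when the physicians conclude that "the subarachnoid space cannot be verifiably reached, and the procedure remains incomplete". A switch of needle is also a failure: the provider's "decision to use other than the assigned spinal needle due to any reason is considered a failed procedure".
- **Data analysis.** The cumulative curve of erythrocyte counts shows proportions of CSF samples, and the incidence of TLP is read from that curve. The efficacy analysis is per protocol, based on the needle actually used. On missing values: "In case of missing data, data estimation nor imputation will not be performed".
- **Secondary outcomes, PDPH.** "The incidence of PDPH will be separately calculated for both study arms using Eq. 3", again over all procedures. Staff contact the family after one week about the diary.

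**The concern.** A procedure with no erythrocyte count can never enter the numerator of Eq. 1 but always enters its denominator. Its effect on the reported incidence is that of a procedure known to be non-traumatic. The same primary quantity therefore has two denominators in one document: all procedures in Eq. 1, and CSF samples in the Data analysis section. They give different answers as soon as one count is missing, and no sentence says which governs.

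The primary noninferiority conclusion is at stake. If uncounted procedures fall mainly in arm A, noninferiority becomes too easy to show. If they fall mainly in arm B, it becomes harder. The Background adds a reason for care: it links repeated attempts with a doubled TLP risk, and cites about a fourfold probability when the first attempt was not successful. Procedures that fail after several attempts may therefore be the more traumatic ones.

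**Working it through.** **Inputs from Data analysis.** Assumed TLP 20% (A) and 30% (B); margin 5 points; about 150 procedures per arm; 90% power; significance level 0.05 with sidedness not stated; decision thresholds of 30 TLPs (noninferiority) and 40 TLPs (superiority) in arm B when arm A has 26/150.

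**Input not in the article.** The number of procedures without a count. I show 3, 8 and 15 of 150 as assumptions.

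**1. The plan's own figures.** With one-sided 0.05,

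n = (1.645 + 1.282)² × (0.20×0.80 + 0.30×0.70) / (0.10 + 0.05)² = 8.56 × 0.37 / 0.0225 ≈ 141 per arm,

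or about 154 with a continuity correction. Power at 150 is 91.5%. The stated figure of about 150 is reproduced. With a Wald upper bound, the threshold of 30 is reproduced at one-sided 0.05 and the threshold of 40 at two-sided 0.05. I therefore use the one-sided 0.05 Wald bound below.

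**2. Effect on the estimate.** Reported incidence = incidence among counted procedures × (1 − share uncounted). A 20% incidence becomes 0.20 × 0.95 = 19.0% with 5% uncounted, and 0.20 × 0.90 = 18.0% with 10% uncounted.

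**3. Effect at the plan's own threshold (26 v 30 TLPs).** Upper bound for A − B = pA − pB + 1.645 × √[pA(1−pA)/nA + pB(1−pB)/nB].

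- Eq. 1: 0.1733 − 0.2000 + 1.645 × 0.0450 = 4.73 points. This does not change however many of arm A's 150 procedures lack a count.
- Counted procedures only: 4.87 points with 1 uncounted in A (26/149), 5.01 with 2 (26/148, noninferiority no longer shown), 5.88 with 8 and 7.01 with 15.

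**4. Error rate and power.** Exact binomial enumeration, 150 procedures per arm, treated as independent, with absence of a count unrelated to TLP status. The false noninferiority columns give the range over true rates of 25% v 20% and 35% v 30%; the power columns use 20% v 30%.

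| Uncounted, A / B | False NI, Eq. 1 | False NI, counted only | Power, Eq. 1 | Power, counted only |
|---|---|---|---|---|
| 0 / 0 | 5.1–5.2% | 5.1–5.2% | 91.5% | 91.5% |
| 3 / 0 | 6.2–6.6% | 5.1% | not run | not run |
| 8 / 0 | 8.6–9.8% | 5.1% | 94.8% | 90.8% |
| 15 / 0 | 13.1–16.1% | 5.1–5.2% | 96.8% | 90.1% |
| 0 / 8 | 2.6–3.1% | 4.7–5.2% | 86.1% | 91.1% |
| 0 / 15 | 1.3–1.9% | 4.6–4.9% | 79.5% | 89.4% |
| 8 / 8 | 5.5% | 5.1–5.2% | 90.9% | 90.1% |
| 15 / 15 | 5.7–6.0% | 5.1% | 90.2% | 88.8% |

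Under these assumptions the counted-only denominator holds the error near 5% throughout. Eq. 1 does so only when uncounted procedures are few or evenly split.

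**The case against.** The best defence is that Eq. 1 is loosely labelled and that a counted-only analysis is intended. The Data analysis section reads the incidence of TLP from CSF samples. Table 2 defines the metric as a yes/no on the erythrocyte count, so a procedure without a count has neither value, and imputation is ruled out. No sentence tells the analyst to score an absent count as no TLP. This is fair, and it may well be the intention. But Eq. 1 is the explicit formula for the primary outcome and nothing limits it to counted procedures, so it still has to be corrected.

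The second defence is rarity. Once CSF flows, the provider is to take a sample in both arms, and laboratories count erythrocytes routinely. The per-protocol rule may remove needle switches. This also stands in part. What remains is failures with the allocated needle and therapy-only procedures, at rates the article does not give.

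A reader might infer that the formula rewards the IQ-Tip system, or lets a device that fails more often pass unnoticed. The article does not support that. It gives no rates of uncounted procedures by arm, and the bias reverses if arm B has more of them. Failed procedures are to be reported for both arms, and Eq. 2 counts a failure as a non-success.

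A reader might also infer that a missing diary is scored as no PDPH. No sentence says so, the one-week contact limits such gaps, and PDPH is a secondary outcome without a formal hypothesis.

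**Conclusion.** Eq. 1 is wrong as written and conflicts with the Data analysis section on both the denominator and the handling of missing data. This is a stated rule for the primary outcome, so it is not a detail that can be left to the statistical analysis plan.

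The practical size is conditional. Under the assumed 3 to 15 of 150 uncounted in arm A only, false noninferiority is about 6–16% instead of about 5%; the same kind of imbalance in arm B costs power. With equal shares the error stays at or below 6.0%. These figures rest on assumed counts, independent procedures, and absence of a count being unrelated to TLP status. The documents establish the inconsistency but not that either arm will benefit. The change should be made because the correction is short and, near the decision threshold, two uncounted procedures are enough to alter the conclusion.

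**What to change.** 1. Define the Eq. 1 denominator as procedures with a CSF erythrocyte count, in line with the Data analysis section.
2. Show the number of procedures without a count by arm beside the primary result, split into failures and therapy-only procedures.
3. Add one sensitivity analysis that scores procedures failed without CSF as TLP. This is needed because the corrected denominator also drops failed procedures, which may be the more traumatic ones. The new denominator alone does not address that.
4. As a minor alignment, base Eq. 3 on procedures with diary or one-week contact data.

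Cost: one changed definition, one sensitivity analysis and a small loss of evaluable procedures. With 15 of 150 uncounted in both arms, power on counted procedures is 88.8% against 91.5% with none missing. No new data collection is needed, since failures are already registered.

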#### Secondary outcomes

Secondary outcomes are the first puncture success rate and the incidence of PDPH related to the LP procedures in both study arms.

The success of performing the procedure at the first attempt is defined by the following conditions: only one skin penetration with the needle is done, an eligible CSF sample is obtained and sent for the laboratory analysis, and/or the intrathecal therapy is delivered, and the primary provider does not change during the procedure. Multiple needle redirections are allowed provided that the needle tip remains beneath the skin. Multiple stylet removals and reinsertions are also allowed.

The percentage proportions of the first puncture success rate will be separately calculated for both study arms using Eq. 2.2$$\mathrm{First\;puncture\;success\;rate}=100\times \frac{\mathrm{Total\;number\;of\;succesful\;procedures\;at\;the\;first\;attempt}}{\mathrm{Total\;number\;of\;all\;procedures}}\mathrm{\%}$$

After each study LP procedure, the local study nurse or investigator will give the patient or parents a diary to be filled for reporting perceived symptoms or complications during the day of the procedure and seven subsequent days. These symptoms and complications include PDPH, headache, nausea, backache, fever, leaking, or inflammation at the puncture site. Conforming to the standard definition, PDPH is a severe headache that worsens in sitting or standing positions, eases after lying down, and occurs within 7 days after the procedure. After the week, the study nurse or investigator will contact the patient or parents and inquire about the diary data.

The incidence of PDPH will be separately calculated for both study arms using Eq. 3.$$\mathrm{Incidence\;of\;PDPH}=100\times \frac{\mathrm{Total\;number\;of\;procedures\;causing\;PDPH}}{\mathrm{Total\;number\;of\;all\;procedures}}\mathrm{\% }$$

#### Other outcomes

Incidences of other complications than PDPH will be evaluated from the information collected into the abovementioned 1-week symptom diaries and hospital electronic health records. After the 4-week follow-up of each study LP procedure, the local study nurse or investigator will search the patient’s electronic health records for potential symptoms, complications, or adverse events that may be related to the LP procedures or the use of the IQ-Tip system. In case of possibly overlapping 4-week follow-up periods, duplicate events are not recorded. Potential causality between the recorded symptoms, complications, or adverse events and the LP procedure or the use of the IQ-Tip system will be evaluated and documented by the local principal investigator using a 4-level scoring system (not related, possible, probable, and causal). If causality is considered possible, the event is recorded for further analysis.

As appropriate for the time point, data on symptoms, complications, device deficiencies, and adverse events immediately after the study LP procedure, during the 1-week (diary) and 4-week follow-ups (hospital electronic health records), will be gathered and their rates will be reported for both study arms.

From the CSF samples, in addition to the erythrocyte count (# of erythrocytes/μL in CSF) needed for the incidence of TLP, leukocyte count (# of leukocytes/μL) and the existence of blasts (yes/no) will be determined. Basic blood tests (# of erythrocytes, hematocrit, hemoglobin, # of leukocytes, # of thrombocytes, and the existence of blasts) will be performed from the peripheral blood samples according to standard sample processing and flow cytometric procedures of the hospitals. These laboratory data will be reported for both study arms.

The number of attempts needed for a successful LP procedure will be recorded for each study procedure. Congruent with the definition of the first puncture success rate, an attempt denotes any new penetration of the skin. Being successful means that, irrespective of the number of attempts, a CSF sample is eventually obtained and/or the intrathecal therapy is performed as appropriate for the given procedure. The number of failed LP procedures will be registered as well. An LP procedure is considered failed if the physician(s), even after multiple attempts, conclude that the subarachnoid space cannot be verifiably reached, and the procedure remains incomplete with the available personnel or equipment due to any reason. Also, the provider’s decision to use other than the assigned spinal needle due to any reason is considered a failed procedure. These procedural outcomes will be reported for both arms.

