Incidence of symptoms, complications, and adverse events	Search from hospital electronic health records	Occurrence (yes/no)	Proportion	Within four weeks after each study LP procedure

As an exploratory analysis, logistic regression analysis will be performed to assess factors that may account for the incidence of TLP, defined as a dichotomous variable (yes/no) by the criterion of ≥ 10 erythrocytes/μL. The TLP values will be obtained from the patients’ 2nd, 3rd, and 4th study LP procedures. The following dichotomous variables (yes/no) will be entered to the model as predictors: whether the preceding procedure was performed with a conventional spinal needle, whether the preceding procedure was TLP, whether the consecutive procedures were performed within a week (≤ 7 days) or two (≤ 14 days), whether the patient was obese (BMI ≥ 30 kg/m^2^), whether the provider was experienced with more than 100 previous LP procedures, and whether the thrombocyte count was less than 50,000 platelets/μL [11, 12, 14, 19]. Estimated odds ratios (OR) of the entered predictors will be reported with 95% CIs. The robustness of predictors and related ORs will be verified by performing both backward and forward regression analyses.

Statistical analyses will be done with a concurrent version of IBM SPSS Statistics for Windows (IBM Corp., Armonk, NY, USA).

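### The protocol is inconsistent on whether by-arm complication rates count all events or only those rated possibly related, and the rater very likely knows which needle was used

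*Protocol article*

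**What the plan says.** The Other outcomes section of the protocol article describes two steps for complications other than PDPH.

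- **Search.** After the 4-week follow-up, a study nurse or investigator searches the health records for symptoms, complications or "adverse events that may be related to the LP procedures or the use of the IQ-Tip system".
- **Scoring.** The possible causal link is "evaluated and documented by the local principal investigator using a 4-level scoring system (not related, possible, probable, and causal"). The rule that follows is: "If causality is considered possible, the event is recorded for further analysis".

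The next paragraph of that section says that data on symptoms, complications, device deficiencies and adverse events from the immediate, 1-week and 4-week time points will be collected and their rates given for both arms. It states no causality condition. Table 2 (Data analysis) lists "Incidence of symptoms, complications, and adverse events" with a yes/no occurrence metric, aggregated as a proportion, again without a causality condition.

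On masking, the Procedures section says: "Because of general anesthesia, the patient is blinded to the allocated spinal needle". Nobody else who assesses or scores events is said to be masked. Under Randomization and allocation, at enrolment "the next available envelope in the order will be opened to reveal the sequence of study LP procedures for the given patient".

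**The concern.** A rule that admits events to analysis by relatedness is harmless for a between-arm comparison only if events pass at the same rate in both arms. Here the pass decision is a judgement, and the person making it appears to know the arm. Enthusiasm for the device, caution about a new device, or habit can each shift the share of events passed in one arm relative to the other. A difference between arms could then reflect attribution rather than complications, and a real difference could be hidden.

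The stakes are moderate. The Background makes comparing the incidence of complications a secondary objective, and the Discussion presents the trial as post-market follow-up that will supply evidence on safety against standard practice. The same outcome also has two definitions in one document, so two analysts following the protocol could report different rates.

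**Working it through.** The protocol states no complication rate and no share of events judged related, so there is no figure to reproduce. The check is mainly a comparison of texts.

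**1. Does a causality condition exist?** Yes. The scale has four levels, the lowest being *not related*, and the rule sends an event forward when causality is thought possible. Read plainly, events scored *not related* do not go forward. The rule names only *possible*; on an ordered scale the sensible reading is *possible or higher*.

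**2. Does the rater know the needle?** The text does not say so, but three statements point that way.
- Only the patient is said to be blinded (Procedures).
- The envelope opened at enrolment reveals the whole alternating sequence and determines the binder of color-coded case report forms (Randomization and allocation).
- Part of the judgement concerns the use of the IQ-Tip system: "adverse events and the LP procedure or the use of the IQ-Tip system will be evaluated". That cannot be judged without knowing whether the system was used.

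**3. Is the condition part of the outcome definition?** The texts disagree.

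| Place | Causality condition? |
|---|---|
| Other outcomes, scoring rule | Yes |
| Other outcomes, next paragraph (rates by arm) | None |
| Table 2, occurrence yes/no | None |
| Procedures A and B, immediate complications on the form | None |

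**4. Which outcomes are touched?**
- Traumatic puncture comes from a laboratory erythrocyte count and is not affected.
- PDPH has its own symptom definition, is collected by diary, and is not said to pass the scoring step.
- Other complications found in the records are affected. Whether other diary items pass the step is not clear.
- Comparisons of other complications are descriptive (Data analysis).

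**5. How could the rates move?** Formula for each arm: reported rate = true rate × share passing the condition. Every input below is assumed.
- True rate 15% in both arms, shares 60% (A) and 40% (B): 0.15 × 0.60 = 9%; 0.15 × 0.40 = 6%.
- True rate 20%, shares 0.7 (A) and 0.9 (B): 14% versus 18%, ratio 0.7/0.9 = 0.78.
- True rate 20%, shares 0.9 (A) and 0.7 (B): 18% versus 14%, ratio 0.9/0.7 = 1.29.
- True rate 20%, shares 0.9 in both arms: 18% versus 18%, no between-arm distortion.

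The spurious ratio equals the ratio of the shares, whatever the common true rate. With about 150 procedures per arm, the standard error of the 14% versus 18% difference is √(0.14 × 0.86/150 + 0.18 × 0.82/150) = 4.2 percentage points, treating procedures as independent. In that example the 4-point distortion is about as large as the sampling error.

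**The case against.** The strongest reply is that the paragraph after the scoring rule already promises rates for both arms without a causality condition, and that Table 2 and the recording of immediate complications agree with it. On that reading the rule merely marks events for closer study. This stands in part. A reader might infer that adverse events enter the analysis *only if* rated possibly related, and the document does not settle that. What remains is the conflict itself, because the scoring rule is written as a condition for further analysis.

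Other points on that side:

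- **Lost events.** A reader might infer that events scored *not related* cannot be re-examined. The documents do not support this: scores are documented, Participant Files are archived for 15 years, and the source is the hospital record. The risk is absence from the analysis dataset, not irrecoverable loss.
- **Asymmetry.** An arm A event can be linked to the puncture or to the device, an arm B event only to the puncture. That is not in itself a bias, since device-specific events can occur only in arm A and counting them is legitimate. The difficulty is judgement made with knowledge of the arm.
- **Diary items.** These are reported by patients or parents, the patient is masked, and the scoring step is not clearly applied to them. This stands and narrows the concern mainly to the record search.
- **Missing levels.** Reading the rule as dropping *probable* and *causal* events would be too literal. This is a wording slip.
- **Condensed article.** Tabulation detail may sit in the full protocol. That would answer a silence, but the article states a rule and conflicting definitions.

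**Conclusion.** The point holds as an inconsistency that the sponsor should resolve, with a possible bias in descriptive safety rates if it is resolved in favour of the causality condition. It rests on one inference, that the local principal investigator knows the needle; this is well supported but not stated.

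If the condition is applied, by-arm rates of complications other than PDPH depend on attribution habits. The direction is unknown and the size cannot be estimated from the documents. The 9% versus 6% and the ratios of 0.78 and 1.29 only show the mechanism. With equal passing shares, both arms' rates fall but their ratio does not change.

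A reader might extend this to the trial's main conclusion. The documents do not support that: the primary outcome is a laboratory count, PDPH is not said to pass the step, and the affected comparisons carry no formal hypothesis.

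**What to change.** 1. Keep every retrieved event in the analysis dataset with its four-level score, including those scored *not related*.
2. Make the main by-arm table all events of the types named in the Secondary outcomes section (PDPH, other headache, nausea, backache, fever, and leakage or inflammation where the needle entered), whatever the score. Draw it from the diaries and from a record search for those types that is not limited to events thought possibly related; otherwise the search itself remains a filter of the same kind.
3. Add a second by-arm table of events scored at least possible, meaning possible, probable or causal, and reword the rule accordingly.
4. Align the Other outcomes section with Table 2, so that one definition governs each table.

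**Cost.** A few more form lines per procedure and one more table. Restricting the main table to the named types limits the load from unrelated chemotherapy events. Treatment, visits and sample size do not change.

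**What it leaves.** The second table still reflects a rater who probably knows the needle; masked scoring of relatedness to the puncture, where feasible, would reduce that. Site staff who know the arm would also still run the record search, although a fixed list of event types leaves them less discretion.
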